**Intervention description {11a}**

The study subjects will be randomly allocated in three treatment arms and divided into two experimental groups (two arms: intervention 1 and intervention 2) and one control group, which will be matched for age and sex using frequency matching method (Figure 1). Each eligible patient in the control arm will be received the standard treatment for COVID-19 (a combination of antiviral drugs) and the usual standard of care according to the protocol of MOHME of Iran. If the proposed standard treatment is changed, all patients will receive a new suggestion for further treatment. Each patient in the intervention 1 group will receive the standard treatment for COVID-19 and dexamethasone, (as described below), during the first 24 hours of admission. The dexamethasone will be administrated base on the level of SpO2. If the level of SpO2 does not improve after 24 hours, IV-IG and interferon-beta will be prescribed as shown below along with dexamethasone administration. In the intervention 2 group, the administration of dexamethasone will be started at the first 24 hours of admission and will be continued until 48-72 hours and the level of SpO2 will be checked. Then, if the level of SpO2 does not improve after that time, IV-IG and interferon-beta will be prescribed as the same.

Drug dosages and duration of the regimes are stated below for each intervention group. The intervention begins with the administration of dexamethasone:

If the percentage of the SpO2 level is between 85 and 90, the dosage will be 4 mg every 12 h,

If the percentage of the SpO2 level is between 80 and 85, the dosage will be 4 mg every 8 h,

If the percentage of the SpO2 level is between 75 and 80, the dosage will be 8 mg every 12 h,

If the percentage of the SpO2 level is less than 75, the dosage will be 8 mg every 8 h.

The doses of IV-IG will be 400 mg/kg once daily for 5 days and interferon-beta will be 7 doses every other day. As a note, before the IV-IG administration, the level of IgA will be checked.

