**Sample size {14}**

Based on the proposed effect size from previous studies (10) and assuming a two-sided 5% significance level and a power of 80%, 35 patients will be our sample size in each group. The target sample size will be 105 critically ill COVID-19 patients, which will be allocated randomly in three trial arms with 35 patients in each group. Patients will be allocated into study groups using a simple randomization method.

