**Recruitment {15}**

On each day of the study, the main internal clinical specialist will examine all newly admitted patients in each morning round and select eligible cases based on the triage, laboratory, and CT-scan findings of the patients. One of the clinical colleagues of the project will put randomly patients in three arms and explain the study plan to the patient and provides the informed consent form. The project's lead executor (the staff member responsible for study) will review the availability of all the necessary facilities and make sure that the study is done properly.

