**Assignment of interventions: allocation**

**Sequence generation {16a}**

Participants will be allocated into either control or intervention groups with a 1:1:1 allocation ratio using a simple randomization method (Figure 1). We will use a computer random number generator to generate a table of random numbers for simple randomization.

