**Concealment mechanism {16b}**

The project's principal investigator (PI) (unblinded member) will do the randomization procedure and check the table of random numbers. The allocation process will be concealed to the physician and researchers. Allocation concealment will be made using an opaque sealed envelope system. For this purpose, the names of the groups will be placed in opaque closed envelopes, and whenever, according to the diagnosis of the physician, one of the patients will be eligible to enter the study, one of the envelopes will be randomly selected.

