**Implementation {16c}**

The PI will do the randomization procedure.The main internal clinical specialist will screen all newly admitted patients in each morning round and selected eligible COVID-19 cases. A site investigator will explain the trial for each potentially eligible patient (or their family) and ask them to participate in the study. The site investigator and two research nurses will record the data of participants into patients’ medical charts and HIS. The project's lead executor will access to the data of participants. Two blinded research nurses will follow up on the visits or phone calls. The project's lead executor will send the data to the study therapist and statistical analyzer who are not involved in the study outcome. Each datasheet form will have randomization number codes. Staff responsible for recruitment and symptom ratings is not allowed to receive information about group allocation.

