**Ethics approval and consent to participate {24}**

The ethics committee of Golestan University of Medical Sciences approved the present trial (Ethics committee reference number: IR.GOUMS.REC.1399.004). All participants will freely complete the written informed consent form before entering the study.

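### The protocol gives allocation rules that cannot all be followed (simple randomisation, age/sex frequency matching, a random envelope pick), and contradicts itself on who allocates

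*Protocol*

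**What the plan says.** **Method of allocation**
- Trial design {8}, Sample size {14} and Sequence generation {16a} all name simple randomisation, and {16a} adds its source: "We will use a computer random number generator to generate a table of random numbers for simple randomization".
- Intervention description {11a} says that the subjects are randomly allocated to the three arms, and adds of the groups: "which will be matched for age and sex using frequency matching method".
- Concealment mechanism {16b} has the principal investigator consult the random number table. It then places the group names in opaque closed envelopes and says that, when a physician finds a patient eligible, "one of the envelopes will be randomly selected".
- Sample size {14} expects 105 patients, "allocated randomly in three trial arms with 35 patients in each group".

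**Who allocates, and when**
- Recruitment {15}: "One of the clinical colleagues of the project will put randomly patients in three arms and explain the study plan to the patient". The same sentence goes on to the consent form.
- Implementation {16c}: "The PI will do the randomization procedure". A site investigator explains the trial and invites participation. The section adds: "Staff responsible for recruitment and symptom ratings is not allowed to receive information about group allocation".
- Ethics approval and consent to participate {24}: "All participants will freely complete the written informed consent form before entering the study".

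The limitations paragraph of the Discussion concedes that opaque envelopes can be subverted and offers only speed as a safeguard.

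**The concern.** Site staff cannot follow all of these instructions. Someone must decide whether the table, the age and sex balance or the hand that picks the envelope determines the arm, and the protocol does not say which prevails. Where that choice is made case by case, the next assignment can be influenced by knowledge of the patient. An unordered pick also leaves no sequence against which assignments could later be audited.

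This matters more here because Who will be blinded {17a} leaves the staff and nurses caring for the patients unblinded. Concealment before assignment is therefore a main protection against selection bias, and analysis cannot reliably repair a compromised assignment afterwards. For the same reason this is not something a statistical analysis plan could settle: how patients are assigned is fixed in the protocol.

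**Working it through.** **1. Do the three methods agree?**
- *Simple randomisation against matching.* Simple randomisation assigns each patient with probability 1/3 per arm, whatever the patient's age and sex and whatever came before. Frequency matching forces the age and sex distributions to agree across arms. To obtain the second, one must depart from the sequence or select who enters. The protocol describes no procedure for either.
- *Table against envelope pick.* A pre-generated table fixes which arm comes next. A random pick from a set of envelopes fixes nothing in advance. The table might have been used to fill the envelopes, but that link is not stated, and neither are envelope numbers or how many envelopes each group has.

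**2. Do the sections agree on who and when?**

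| Section | Who allocates | Order relative to consent |
|---|---|---|
| Recruitment {15} | a clinical colleague, who also explains the study and provides the form | allocation is mentioned first |
| Concealment mechanism {16b} | the principal investigator | envelope drawn on eligibility; consent not mentioned |
| Implementation {16c} | the principal investigator; recruiting staff may not know the allocation | not stated |
| Ethics approval {24} | not stated | consent before study entry |

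Under {15} one person both recruits and allocates. Under {16c} that is not allowed. Both cannot be followed.

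**3. Does simple randomisation give 35 per arm?**

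Inputs: 105 patients and a 1:1:1 ratio ({14}, {16a}). The plan's total agrees: 3 × 35 = 105.
- P(35/35/35) = 105! / (35!³ × 3¹⁰⁵) = 0.0078, or 0.8%.
- One arm has SD √(105 × 1/3 × 2/3) = 4.8 and a central 95% range of 26 to 45.
- Summing the exact multinomial distribution: expected smallest arm 30.0, expected largest arm 40.0, P(smallest ≤ 30) = 51%, P(largest − smallest ≥ 10) = 49%.

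**4. What does that cost in power?**

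The protocol cites an effect size but gives no value, so 35 per arm cannot be reproduced. As an assumption, I solve for the standardised difference d that 35 per arm detects with 80% power at two-sided 5%:

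d = (1.960 + 0.842) × √(2/35) = 0.67

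Power for arms of n₁ and n₂ is Φ(d / √(1/n₁ + 1/n₂) − 1.960):

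| Arms compared | Power |
|---|---|
| 35 v 35 | 80.0% |
| 30 v 40 | 79.2% |
| 30 v 35 | 76.8% |
| 28 v 42 | 78.4% |
| 25 v 45 | 76.6% |

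The loss is about 1 to 3 points. A pair made of the two smaller arms in a less balanced split, 28 v 35, has 75.2%, a loss of about 5 points, while the comparisons with the largest arm lose less or gain.

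**The case against.** Four objections deserve an answer.

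1. *Allocation before consent is not established.* A reader might infer from Recruitment {15} that the recruiting clinician allocates first and seeks consent afterwards, so that patients could refuse knowing their arm. The documents do not support that as fact. It rests on word order in one sentence, nothing says that the arm is disclosed before consent, {24} puts consent before entry, and {16b} and {16c} give the task to the principal investigator. This objection stands: the finding is a contradiction over who allocates and an unclear order.

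2. *35 per arm may still be reached.* A reader might infer that none of the described methods can give 35 per arm. The calculation shows this for simple randomisation only. A closed set of 105 envelopes, 35 per group, drawn without replacement would give 35/35/35 exactly. That stands, although the stock is not stated and such a scheme is not simple randomisation. Unequal arms from simple randomisation also cause no bias, and the power cost is small.

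3. *The table may feed the envelopes.* {16b} mentions both, and the allocation flow chart (Figure 1) is not available here. It is therefore right to say that the link is unstated, not that the table is ignored. The matching conflict does not depend on this.

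4. *The risk is disclosed.* The Discussion admits possible subversion. Disclosure does not resolve the contradictory instructions, and speed is not a control.

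Nor is the absence of stratification by hospital an error. Unstratified randomisation is valid, and the protocol promises no balance within hospitals.

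**Conclusion.** The protocol is wrong as written. Simple randomisation and frequency matching on age and sex cannot both be carried out, the envelope pick has no stated connection to the table, and the sections disagree on who allocates and on whether that person may also recruit. These conclusions rest on the text alone.

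The consequence is a risk of selection bias from an allocation that cannot be audited and can be subverted. The documents do not show that bias has occurred, and its size cannot be calculated from them.

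The arm-size point is secondary. It assumes simple randomisation of exactly 105 patients, and the power figures assume d = 0.67, which is back-solved and not stated in the protocol.

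**What to change.** State one mechanism and use it throughout:
- a computer-generated permuted-block list with varying block sizes in multiples of three, placed in sequentially numbered, opaque, sealed envelopes;
- each envelope opened strictly in order, and only after eligibility and signed consent have been recorded;
- the list held by a role without patient contact and separate from those who recruit, for example the unblinded pharmacist already described in {17a}.

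Delete the frequency-matching wording in {11a}, the random envelope pick in {16b} and the wording in {15} that has the recruiter allocate. Then make {8}, {11a}, {14}, {15}, {16a}, {16b} and {16c} agree.

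If the blocks are chosen to sum to 105, a single list gives 35 per arm once all are enrolled. Stratifying by hospital is optional, and incomplete blocks could then leave small departures from 35. Adjusting the analysis for age, sex and entry SpO2 is also optional; it would serve the apparent purpose of the matching without touching the allocation.

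**Cost.** The drafting and the list are cheap, and no new role is needed. However, Trial status gives the trial as recruiting, from April 18 2020 with an expected end of June 19 2020. The change is therefore an amendment that needs registry review and prior ethics approval under {25}. It can apply only to patients not yet allocated. The method actually used for earlier patients must be documented and reported.

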**Criteria for discontinuing or modifying allocated interventions {11b}**

Participants can/will be withdrawn from the study if the patients or their families request to be excluded from the study or the study is thought to be dangerous for the patient or the risks are more than the potential benefits.

If signs of severe respiratory infections appear, treatment will be based on the doctor's opinion and the condition of each patient; as well as, the subject will be immediately withdrawn from the study. However, the patient's information will be collected in such unforeseen and adverse events and studied.

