**Who will take informed consent?** **{26a}**

The potential trial participants will sign the informed consent form if they have decision-making capacity. In the situation of the participants are unable to fill out the form, an independent clinician will confirm in writing that the participant cannot fill out the form. Therefore, her/his authorized family will be informed of the study and will be told all the advantages and disadvantages of the study and they will have the free right to include their patient to the study. Whenever the patient gains his ability and consciousness to decide, she/he will be notified of the nature of the study and has the option to stay in the study or withdraw from the study. Based on the request of participants all collected data will be deleted.

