**Plans to promote participant retention and complete follow-up {18b}**

All related data about the outcomes including the daily level of SpO2, vital status, intubation status, the hospital stay length, and the time of discharge will be obtained during the hospitalization, day 14, and followed up one month after the discharge time. The data will be obtained by HIS, physical visit on a bed or a telephone interview. The main coordinator will provide written feedback and send an acknowledgment to the participants or their families. Besides, all cases who withdraw their study participation will be followed one month and If they need management and health services, they will be taken care of. Moreover, information from people who have dropped out of the study will also be checked if they have received enough doses of the drugs and will not be replaced by other patients.

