**Methods in analysis to handle protocol non-adherence and any statistical methods to handle missing data {20c}**

Any missing data in the HIS information will be completed by a telephone interview, if possible. Protocol modifications and study subjects' replacement will not be expected. All primary and secondary outcomes, as well as adverse events, will be done as the intention-to-treat principle.

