**Discussion**

There are many questions about the treatment and effectiveness of used drugs in this COVID-19. Regarding the treatment of the disease, the issue of ARDS and Cytokine storm should be considered. ARDS acts as an important cause of death in critically ill patients of COVID-19. Cytokine storm and inflammatory mediators are two main suspects for this condition (3,4). All of these can lead to lung damage. Therefore, before extensive damage to lung tissue, clinical therapies should be considered on the control of the responses of the immune system and suppressing the inflammation, in critically ill patients. Theoretically, corticosteroids could help to reduce the incidence of ARDS and consequently the mortality rate (4). But their therapeutic effects and advantages and disadvantages are still in the mist.

Results of previous experiences in influenza and SARS and little new experiences in the management of COVID-19 are inconsistent, especially about the prescription time and number of corticosteroids in different phases of ARDS in the diseases. Use of corticosteroids in all cases of influenza or both SARSs may lead to secondary superinfections and increase mortality rate (12) and patients should be monitored very carefully and the medication should be given at the appropriate time. Besides, high-doses corticosteroids therapy may induce a worse outcome (13). However, the aggregation of the results of different studies indicates an improvement in disease outcomes using early doses of corticosteroids in critically ill patients. One systematic review evaluated the results of ARDS patient data from randomized trials and showed prolonged corticosteroid treatment improved clinical outcomes (14,15). Another randomized controlled trial study showed that corticosteroid therapy could down-regulate inflammation mediators in ARDS and reduce the duration of mechanical ventilation and staying in ICU (14). Surviving Sepsis Campaign has also recommended the use of corticosteroids if the patient is in the cytokine storm condition and if the patient has not yet developed ARDS (16). Some experiences from SARS showed that convalescent plasma or IV-IG can improve the survival rate of patients when they were treated with pulsed methylprednisolone. In this regard, we can use IV-IG to reduce the side effects of corticosteroids (15).

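### Withdrawal from the study on an undefined respiratory trigger, an unclear dose condition and data deletion on request conflict with the promised intention-to-treat analysis and risk informative exclusion of non-responders

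*Protocol*

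**What the plan says.** Four sections of the protocol bear on who stays in the analysis.

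- **Section {11b}**, on discontinuing or modifying the interventions: "If signs of severe respiratory infections appear, treatment will be based on the doctor's opinion and the condition of each patient", and "the subject will be immediately withdrawn from the study". The next sentence adds that "the patient's information will be collected in such unforeseen and adverse events and studied".
- **Section {18b}**, on retention: "all cases who withdraw their study participation will be followed one month". Information from people who dropped out "will also be checked if they have received enough doses of the drugs", and they are not replaced. What counts as sufficient dosing is not stated.
- **Section {26a}**, on consent: "Based on the request of participants all collected data will be deleted". The sentence follows the text on patients who regain capacity and may then stay or leave.
- **Section {20c}**, on non-adherence and missing data: "All primary and secondary outcomes, as well as adverse events, will be done as the intention-to-treat principle". The only stated remedy for missing data is a telephone interview, where possible.

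The primary outcome in {12} is whether a patient's SpO2 rises above 90%. Intubation, freedom from ventilation and mortality are secondary outcomes. According to {11c} and {17a}, prescribers and care staff know the allocation, while those who measure outcomes do not.

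**The concern.** Intention-to-treat needs each randomised patient to be followed and counted in the allocated arm, whatever happens after randomisation. Section {11b} ties leaving the study to a clinical event after randomisation. Under the definition in {10}, patients enter with SpO2 below 90% and rapid breathing, or with more than half of the lung involved. In such patients the trigger can hardly mean anything but worsening or a superimposed infection, and both bear directly on the outcomes.

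The trigger is not defined, and staff who know the allocation manage the patients, so it could be applied differently by arm. A condition on doses received would select on another post-randomisation variable, and deletion would take some patients out for good.

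If the team follows these rules literally, the patients missing from the comparison may be mainly those who did not respond. With 35 per arm, a handful of such exclusions is enough to shift the result.

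**Working it through.** **1. The plan's own figures.** Section {14} gives 35 per arm and 3 × 35 = 105, which is correct. It states no response rate and no allowance for losses, so any response rate used below is an assumption.

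**2. The sections side by side.**

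| Section | Effect if followed literally | Fit with {20c} |
|---|---|---|
| {11b}, withdrawal sentence | Patient leaves the study on the trigger | Conflicts |
| {11b}, next sentence | Information is still collected and studied | Compatible, but silent on arm and scoring |
| {18b}, follow-up sentence | Withdrawn cases are followed for one month | Compatible, but oximetry after withdrawal is not specified in that sentence |
| {18b}, dose sentence | Either a filter on dropouts' information or an added check of their dosing | Conflicts on the first reading only |
| {26a} | All data erased on request | Intention-to-treat is impossible for those patients |

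Intention-to-treat therefore remains feasible except where data are deleted. The text does not settle whether a withdrawn patient is counted in the allocated arm, or how that patient is scored on SpO2.

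**3. What exclusion would do (illustration only).** Assume no true effect, 35 per arm and a response rate of 50% in both arms. The expected number of responders per arm is 35 × 0.50 = 17.5, and of non-responders also 17.5.

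- Five non-responders left out of one arm: 17.5 / (35 − 5) = 17.5/30 = 58.3%, against 17.5/35 = 50%. The spurious difference is 8.3 points, in favour of whichever arm lost them.
- Five left out of each arm: 58.3% in both. There is no spurious difference, but both rates are overstated.

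**4. Range.** If a share f of non-responders is left out, the observed rate is p / (p + (1 − p)(1 − f)). For p = 0.50 and f = 0.20 this is 0.50/0.90 = 55.6%; for f = 0.40 it is 0.50/0.80 = 62.5%. The table takes true rates of 40% to 60%, equal in both arms. The last column is the chance of a significant result at a nominal two-sided 5%, by normal approximation.

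| Share of non-responders left out | Spurious difference | Chance of significance |
|---|---|---|
| 20% in one arm only | 5 to 6 points | about 7% |
| 40% in one arm only | 11 to 13 points | about 16% |
| 20% in one arm, 40% in the other | 6 to 7 points | about 8% |
| Equal in both arms | 0 | 5% |

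The five-patient example is 5/17.5 = 28.6% of non-responders, inside this range.

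**5. With everyone retained.** If the five patients stay in the denominator as not having reached the target, the rate is 17.5/35 = 50% in both arms and the spurious difference disappears.

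**The case against.** The strongest reply is that the protocol never excludes anyone from the analysis. Section {11b} sits under a heading about interventions, and its next sentence keeps collecting the withdrawn patient's information. Section {18b} follows withdrawn cases for a month without replacing them, and {20c} applies intention-to-treat to all outcomes. Analysis sets and scoring rules are often left to a statistical analysis plan, which is not at hand. The dose sentence may only mean that dosing will be verified. This stands in large part. A reader might infer that failures are removed and that intention-to-treat is defeated; the text does not support that.

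The reply does not remove the conflict. Who leaves the study, what is measured afterwards and what is erased are protocol and consent rules. A later analysis plan cannot recover deleted or unmeasured data.

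Other stronger readings also fail:

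- **Bias towards the steroid arms.** The Discussion says that corticosteroids "may lead to secondary superinfections and increase mortality rate", but of their use in all cases of influenza or SARS, and the same paragraph goes on to report better outcomes with early doses in critically ill patients. If dexamethasone works as hypothesised, more controls might meet the trigger, and the bias would run the other way.
- **Concealed harm.** Section {22} sends adverse events to the steering and ethics committees and has causes of death investigated.
- **Controls or early deaths cannot satisfy the dose condition.** Controls receive antiviral drugs under {11a}, {17a} mentions coded control drugs, and death is an outcome in {12}, not stated to be a dropout.
- **Deletion removes failures.** Deletion follows a request. Nothing ties it to arm or outcome.

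**Conclusion.** The point holds as an internal conflict with a real risk attached. The withdrawal sentence in {11b}, the dose sentence in {18b} on one of its readings, and the deletion sentence in {26a} do not fit the intention-to-treat promise in {20c}. The withdrawal sentence also sits badly with the continued collection and follow-up promised in {11b} and {18b}. Because its trigger is undefined, close to the outcomes and in the hands of staff who know the allocation, following the text literally could exclude non-responders informatively.

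The direction of any bias is uncertain. Its size cannot be derived from the protocol. The 58% against 50% rests on an assumed 50% response, on all five withdrawn patients being non-responders, on losses in one arm only, and on their being dropped from the denominator, which the protocol nowhere states. Equal losses would give no spurious difference in that setting.

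**What to change.** Reconcile {11b}, {18b}, {20c} and {26a}.

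- **Withdrawal.** Separate discontinuing the allocated treatment from leaving the study. When and how treatment is discontinued stays with the investigators; no change to that clinical rule is proposed here.
- **Analysis.** State that every randomised patient remains in follow-up and is analysed in the allocated arm. Score withdrawn patients by their observed outcome or, if SpO2 is not observed, as not having reached more than 90%.
- **Dose condition.** Delete it from {18b}, or confine it to a per-protocol sensitivity analysis labelled as such, with the required dosing defined.
- **Deletion.** Limit it to what consent requires, keep data collected up to withdrawal where consent allows, and report the number of deletions by arm.

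The cost is wording in the protocol and the consent form. Follow-up of withdrawn patients is already planned in {18b}.
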